### Analysis

To assess the effect of the SP intervention, group differences on the primary and secondary outcome measures will be examined using a series of mixed-effects repeated measures (MMRM) models, which will specify timepoint, participant, and condition as levels in the analyses. MMRM is a full-information maximisation likelihood estimation strategy that can model data even when some observations are missing, and thus honours the intention-to-treat principle [50]. For all hypothesis testing, both intention-to-treat analyses (ITT; where all available data are included in MMRM) and per-protocol analyses (PP; only including participants who met eligibility criteria throughout the trial period, completed the intervention according to the protocol and had both baseline and follow up data) will be completed. Furthermore, we will test the extended Social Identity Model of Identity Change (Fig. 1) using a structural equation modelling approach that accounts for nested data (i.e., individuals within group programs) to test relationships across time between group membership, new group identification, old and new group compatibility, help given to others in the group, interpersonal emotion regulation, and the outcomes of loneliness, wellbeing, and health service use.

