### Measures

***The primary outcomes are loneliness, wellbeing, and health service use, and these will be assessed in both T1 and T2 surveys.***

*Loneliness* will be assessed via the 8-item brief UCLA Loneliness Scale [45] (e.g., ‘how often do you feel left out?’), in which responses are made on a 4-point scale (where 0 = *never*, 1 = *rarely*, 2 = *sometimes*, and 3 = *often*). Items are summed to produce a total score ranging from 0 to 24.

*Wellbeing* will be measured using the 14-item Warwick Edinburgh Mental Wellbeing Scale [46]. The items are positively worded and ask respondents how often they have experienced various psychological states over the past 2 weeks (e.g., ‘I’ve been feeling relaxed’) on a 5-point rating scale (where 1 = *none of the time* to 5 = *all of the time*). Scores are summed to produce a total score in the range from 14 to 70, with higher scores corresponding to a higher level of mental well-being. The WEMWBS is psychometrically robust in general populations, with excellent internal consistency (α = 0.91) and good test-retest reliability (*r* = .83) [46].

*Health Service Use* will be measured by the self-reported total number of visits that participants make to hospital, community mental health services, counsellor, psychologist, psychiatrist, social worker, GP (in person, over the phone, or via home visit) over the course of the study (adapted from the measure used in [47]). In addition, respondents will be asked to rate their current health on a single 5-point scale (where 1 = *very poor* to 5 = *very good)*.

Secondary outcomes are process measures by which the social prescribing intervention is expected to produce effects on the primary outcomes: group memberships and identities, new group identification, former and new group compatibility, and group-based psychosocial resources of social support and emotion regulation.

*Group memberships and identities* Participants will be asked to list up to six groups that they are members of and rate the importance of each on a 7-point scale (where 1 = *not important* to 7 = *very important).* From this, the number of important groups (i.e., those rated 5–7) will be derived (see [34], p. 350–351).

*New group membership and identification* Social identification with the (first) new group that the participant has joined through the social prescribing program will be measured by 4-items rated on a 5-point scale (where 1 = *strongly disagree* to 5 = *strongly agree* [48];).

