*Group compatibility* will be measured by averaging 2 items: ‘Being a member of my new group/s is compatible with being a member of my other groups’ and ‘The norms and values of my various groups are compatible with each other’, both rated on a 5-point scale (where 1 = *strongly disagree* to 5 = *strongly agree* [34];, pp. 349–350).

*Group-based psychological resources* are defined as social support received and provided, measured by an average of scores on 2 items from [43]: ‘I get support from people in my new group’ and ‘I provide support to others in my new group’. Each is rated on a 5-point scale (where 1 = *strongly disagree* to 5 = *strongly agree*). Emotion regulation was measured using a 12-item version of the Emotion Regulation of Others and Self measure [49], which has been validated in previous research using a large sample representative of the UK population [42]. In this study, we use the two interpersonal EROS subscales assessed by 3 items each: extrinsic affect improving (e.g., ‘I discussed someone’s positive characteristics to try to improve how they felt’) and extrinsic affect worsening (e.g., ‘I explained to someone how they had hurt myself or others to try to make the person feel worse’).

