## Discussion

This project will represent the first controlled evaluation conducted in Australia - a country where such prescribing is only emerging [20, 21]. It will also be one of the few studies that adopts a social cure theoretical framework [33, 34] to understand the processes through which social prescribing to community group activities produces expected changes in loneliness, wellbeing, and health service use (see also [23, 38] in the UK). The wide range of self-report measures and link worker collected service data will provide a rich data set. Specifically, between the two assessments, we expect to find improvements in well-being and reduced loneliness among those engaging with the intervention, and minimal change in these outcomes for participants in the TAU condition.

In line with social cure theorising, and our extended SIMIC-based model of social prescribing, we expect improvements associated with joining a new group activity through social prescribing to be mediated by new group identification, old and new group compatibility, and group based psychological resources which are gained. These changes are expected to contribute to reduced health service use at follow-up, as has been observed in previous research in which adults who frequently attend GP clinics met their social needs through meaningful group participation [10].

The findings will be disseminated via a final report, a summary communicated to the participants and stakeholders by email, and in scholarly publications and presentations. They will inform policy and practice developments in the community and health sectors in Queensland and potentially have impact across Australia and beyond. This research is timely, as there have been growing calls for policy- and evidence-based interventions to address social isolation and loneliness, especially in the wake of the COVID-19 pandemic and related social distancing and lockdowns [51–54]. The absence of high-quality evidence and a rigorous theoretical framework is the primary barrier to wider implementation of a social prescribing approach and this study fills both of those gaps.

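### The between-arm MMRM is applied to every secondary outcome, but new-group identification is undefined in TAU and the other new-group items have no meaningful TAU comparison, so condition effects on them, and mediation of the SP-versus-TAU effect through them, are not identified

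*Protocol article*

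**What the plan says.** All references are to the protocol article.

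- **Analysis.** The plan is that "group differences on the primary and secondary outcome measures will be examined using a series of mixed-effects repeated measures (MMRM) models". Condition and timepoint are both factors in these models, and no secondary outcome is excepted. A separate structural equation model (SEM), allowing for nesting of individuals in group programs, is to test the extended SIMIC model. The section does not say which arms enter it.
- **Measures.** The secondary outcomes are "group memberships and identities, new group identification, former and new group compatibility, and group-based psychosocial resources of social support and emotion regulation".
  - Identification is "Social identification with the (first) new group that the participant has joined through the social prescribing program".
  - Support averages two items, on support received and support given, both about the new group. The second reads "I provide support to others in my new group".
  - Compatibility averages two items. The first is "Being a member of my new group/s is compatible with being a member of my other groups"; the second asks about the respondent's various groups in general.
- **Data collection.** SP participants complete T1 around the time they start meeting the link worker, either before their first group session or shortly after it. TAU participants stay on usual primary care for the same 8 weeks.
- **Design and participants.** TAU participants are patients who have not been referred to a social prescribing scheme.
- **Discussion.** On mechanism: "we expect improvements associated with joining a new group activity through social prescribing to be mediated by new group identification", and also by compatibility and group-based resources.

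**The concern.** The Analysis section fixes a comparison that the Measures section rules out for some of the outcomes it covers. A participant who was never referred to social prescribing cannot report identification with a group joined through it. The article notes that MMRM can handle missing observations, but that does not help here: the value does not exist for anyone in the arm, so there is nothing for the likelihood to borrow from.

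What is at stake is the second aim, which is how social prescribing works. If the new-group measures are analysed in the only arm that has them and the result is then described as mediation, a within-arm association could be read as the mechanism behind the difference from TAU.

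**Working it through.** **1. The plan's own figure.** The Power calculation section gives 90 participants, 45 per condition, for f = .30, power 0.8 and alpha .05. A two-group F test at one time point has noncentrality f² × N = 0.09 × 90 = 8.1 on 1 and 88 degrees of freedom, and power 0.804. So 90 reproduces. This point is about estimability, and the sample size neither supports nor refutes it; it supplies only the 45 per arm used in step 5.

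**2. Which process measures are defined where.**

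| Measure | TAU | SP at T1 | SP at T2 |
|---|---|---|---|
| Number of important groups | yes | yes | yes |
| Emotion regulation (two EROS subscales) | yes | yes | yes |
| Compatibility, item 2 | yes, for anyone with groups | yes, for anyone with groups | yes |
| Compatibility, item 1 | only if a group is joined independently | absent or partial | yes |
| Support, both items | only if a group is joined independently | absent or partial | yes |
| New-group identification | undefined | absent or partial | yes |

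SP at T2 assumes that the participant joined a group. The article states collection at both T1 and T2 explicitly only for the primary outcomes, so the entries show where a measure could be answered.

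**3. Estimability of the MMRM contrasts.** The fixed effects are intercept, condition (C), time (T) and C × T. The row for each cell is [1, C, T, C×T]:

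- TAU T1: [1, 0, 0, 0]
- TAU T2: [1, 0, 1, 0]
- SP T1: [1, 1, 0, 0]
- SP T2: [1, 1, 1, 1]

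With all four cells filled the rank is 4 of 4. With both SP cells only, the rank is 2: the intercept and C columns are identical, and so are the T and C×T columns. With SP at T2 only, the rank is 1. In both SP-only cases neither the condition effect nor the condition-by-time effect is estimable. New-group identification falls in these cases whether or not some SP participants have a T1 value.

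**4. Mediation.** An indirect effect of condition is a × b, where a is the condition-to-mediator path and b the mediator-to-outcome path. The design for a is [1, C]. With SP data only, C is constant and the rank is 1 of 2, so a is not identified. Path b is estimable within SP, for example from

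outcome(T2) = β0 + β1 × outcome(T1) + β2 × mediator(T2) + error,

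but β2 is an association within one arm and does not decompose the SP-versus-TAU difference.

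**5. Precision of what remains.** The smallest single correlation detectable with 80% power at two-sided 0.05, by Fisher's z, is r = tanh[(1.960 + 0.842) / √(n − 3)]:

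- n = 90: tanh(2.802 / √87) = tanh(0.300) = 0.29
- n = 45: tanh(2.802 / √42) = tanh(0.432) = 0.41

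This makes no allowance for clustering within group programs or for SP participants who join no group. Either would normally make it worse.

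**The case against.** The strongest reply has four parts.

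- **The SEM is separate from the MMRM.** The variables listed for it do not include condition, nesting within group programs suits an SP-only model, and the Discussion speaks of improvements associated with joining a group. On that reading no decomposition of the SP-versus-TAU effect is expressly promised. This stands in part. A reader might infer that the mechanism aim as a whole cannot be met, and the article does not support that: within-SP paths are estimable, and paths through number of important groups and emotion regulation can use both arms. But the arms entering the SEM are not stated, and the Discussion's language of mediation invites the between-arm reading.
- **The new-group measures are not all empty in TAU.** A reader might infer that TAU has no data on support or compatibility. Only identification is tied to the program by definition. A TAU participant who joins a group independently could answer the support items and the first compatibility item, and the second compatibility item needs no new group. This stands, but comparing SP with a few self-selected TAU joiners would not be a meaningful between-arm test.
- **SP baseline is not wholly missing.** Some SP participants will have just started a group at T1, and the article gives no proportion. This stands. A claim that these measures exist only for SP at T2 would go too far, although filling SP at T1 does not restore the condition contrast.
- **A condensed article may leave to a fuller document which arm answers which item.** This does not meet the point. The article does not merely omit a detail; it states an analysis for all secondary outcomes that its own definition of identification excludes.

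A count of SEM parameters against 45 people would prove nothing either way, because the path diagram (Fig. 1) is not shown.

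**Conclusion.** The point holds in limited form. For new-group identification, the stated MMRM comparison is not estimable (rank 2 of 4 at best). For support and the first compatibility item it has no meaningful TAU side, and the planned two-item compatibility score inherits the problem through that item. Mediation of the SP-versus-TAU effect through these variables is not identified. Within-SP associations on about 45 people can be estimated, with a smallest detectable correlation of about 0.41.

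The primary outcomes, number of important groups, the emotion-regulation subscales and the second compatibility item are not affected.

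This rests on two assumptions: that identification is collected as defined, with no TAU version, and that few TAU participants join a new group independently. The second matters only for support and compatibility. The passages should be reconciled, but nothing here touches the primary comparison, so this is a should-fix.

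**What to change.** 1. Limit the between-arm MMRM to process measures defined in both arms at both times: number of important groups, the two EROS subscales, and the second compatibility item on its own. State that these are collected at T1 and T2 in both arms.
2. Test mediation of the condition effect only through those measures.
3. Analyse new-group identification, support and the new-group compatibility item in the SP arm only. Relate their T2 values to the T2 outcome adjusted for the T1 outcome, and report the results as associational, not as mediation of the intervention effect.
4. State that the new-group part of the SEM uses SP participants only, and align the Discussion's wording on mediation with that.

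The cost is a few sentences of analysis text, a one-item instead of a two-item compatibility measure in the between-arm comparison, and a weaker claim about mechanism. No new data and no change in sample size are needed. Rewording the support items so that both arms can answer is not a clean alternative: registration was retrospective, so data collection had probably begun, and two versions of the items, measuring different constructs, would be mixed.

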## Methods

### Design and participants

While a randomised controlled design would be the strongest methodology, it requires participants to be interested and available to attend sessions with a link worker and then group activities as part of the social prescribing intervention if they are allocated to the treatment condition. It would be difficult to retain participants in social prescribing who are not interested and/or available, and conversely, it would be unethical to withhold social prescribing from participants who are interested and available, given evidence that it is potentially effective in managing loneliness. Accordingly, as shown in Fig. 2, our study will have a non-randomised controlled (parallel) design, with a social prescribing condition (SP) and a primary care treatment as usual (TAU) condition.

This research will take place in 5 sites in Southeast Queensland where social prescribing is offered, using a combination of GP and community centre models. The sites are in areas with diverse populations in terms of socioeconomic and cultural backgrounds: a community centre in a southern suburb of Brisbane, a GP clinic in the same suburb, a GP clinic in a southwestern suburb of Brisbane, a community centre in a northern suburb of Brisbane, and a combined GP and community centre in a regional city located about an hour’s drive south of Brisbane.

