*Social Prescribing participants* (SP) will be adults aged 18 and over, experiencing loneliness or social isolation who are eligible for referral to the social prescribing programs at these sites. Local General Practitioners and Allied Health Professionals expected to be the most likely referral pathway. Recruitment will be promoted through the authors giving talks to referring agents and through project steering meetings. Participants will have sufficient English language skills to be able to provide consent to participate in the research. We expect them to range in age, and to represent a variety of cultural and ethnic groups. Exclusion criteria are that the individual reports acute symptoms (such as suicidal ideation, manic or agitated behaviour, or intoxication), or an acute social issue (such as domestic violence or housing crisis that would need to take priority), that would interfere with their capacity to engage with SP. Such individuals will be directed by the Link Worker to a more suitable service. Link Workers will refer clients who indicate an openness to participating the study to the researchers who will contact individuals to confirm their consent to participate in the study.

*Treatment as Usual participants* (TAU) will be selected from GP clinics in the same locations as the social prescribing programs and will meet our inclusion and exclusion criteria. A staff member within each of these services will identify frequent attending patients who will be contacted by telephone by the researchers and invited to participate in the study. Frequently attending patients will be defined as patients attending the practice 12 or more times each year over a two-year period who have not already been referred to a social prescribing scheme. These parameters remove patients attending frequently for short-lived medical needs, such as a pregnancy. We will assess for baseline differences between the conditions and statistically control for any variables that are found to differ significantly at baseline.

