### Power calculation

An a priori power analysis indicates that a sample size of 90 would be required to detect a significant difference between groups with a medium effect size (*f* = .30) on primary outcome variables, with a power of 0.8 and a default alpha of .05, using the planned 2 X 2 mixed analysis of variance. Our goal for recruitment is therefore to continue until we reach 90 with data at both time points (i.e., 45 in each condition).

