### Data collection

Data will be collected via survey by researchers either in-person or online when in-person data collection is not feasible. Participants will be allocated a study code so that no identifying information is collected with the surveys. The initial (T1) survey will be collected when participants first engage in social prescribing (i.e., when they begin to meet with the Link Worker, but are yet to attend a group or have only recently started attending a group activity). Participants will then be followed up 8-weeks later (T2). The number of group activities a participant joins during the 8-week period is up to the discretion of the participant and Link Worker, however, we expect that this will typically be just one new group. Surveys will be collected from the TAU participants across the same time interval of 8 weeks, and they will continue to receive primary care treatment as usual. Participants will be reimbursed with AUD $40 vouchers at T1 and T2. Non-identified service audit data will also be collected by researchers from the Link Workers to gain an overall sense of the total number of program referrals and the different referral pathways, as well as general demographic characteristics.

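### The primary MMRM leaves out the group-program clustering that the SEM allows for, so the standard error of the SP effect is too small if 8-week outcomes correlate within groups

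*Protocol article*

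**What the plan says.** The Analysis section describes the models for the primary and secondary outcomes as mixed-effects repeated measures models "which will specify timepoint, participant, and condition as levels in the analyses". No group program and no site is listed.

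Later in the same section, the extended SIMIC model is to be tested with a "structural equation modelling approach that accounts for nested data (i.e., individuals within group programs"). Nesting is thus planned for the mechanism analysis, and for group programs only.

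Three other places bear on the point:

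- Data collection says of the number of groups joined in the 8 weeks: "we expect that this will typically be just one new group".
- Design and participants states: "This research will take place in 5 sites in Southeast Queensland where social prescribing is offered". It adds that TAU participants "will be selected from GP clinics in the same locations as the social prescribing programs".
- Power calculation sizes the study at 90, 45 per condition, "with a medium effect size (*f* = .30) on primary outcome variables", "with a power of 0.8 and a default alpha of .05". It makes no allowance for clustering.

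**The concern.** SP participants who attend the same group are unlikely to be independent at T2. The article's own theory, in the Background, is that benefit comes from identifying with a shared group and from the support and emotional sharing among its members. If that is right, members of one group should move together. The T1 survey is taken before or soon after group attendance starts, so most of this shared influence would appear at T2 and therefore in the change that the trial tests.

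TAU participants are not placed in groups, so the clustering falls on one side of the comparison and inflates the variance of the SP-TAU contrast. A model that knows only timepoint, participant and condition does not see this. Its confidence intervals for loneliness, wellbeing and health service use would be too narrow, and the false positive rate would exceed the nominal 5%.

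**Working it through.** **Step 1: reproduce the plan's sample size.** Inputs from Power calculation: f = 0.30, power 0.80, alpha 0.05, N = 90. For two equal groups d = 2f = 0.60. With a noncentral F for two independent groups and one measure, lambda = N × f² = 90 × 0.09 = 8.1 on 1 and 88 degrees of freedom, and power is 0.804. N = 90 is the smallest even total that reaches 0.80. Versions with two correlated measures do not give 90: at a correlation of 0.5 the between-subject effect needs 68 and the interaction 24. The stated 90 therefore matches a two-group comparison of independent participants. The normal approximation used below gives 0.812 at 45 per arm.

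**Step 2: variance with clustering in the SP arm only.** Let m be the number of study participants per group and ICC the within-group correlation of the outcome analysed (T2 outcome or change). Neither is in the article, so both are assumptions.

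- SP design effect: DE = 1 + (m − 1) × ICC; TAU has 1.
- True SE divided by model SE: R = √((DE + 1)/2).
- True type I error of a nominal 5% test: 2 × (1 − Φ(1.96/R)).
- Power of a test with the correct SE, 45 per arm: Φ(0.60/√((DE + 1)/45) − 1.96).

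Worked example, m = 9 and ICC = 0.10: DE = 1 + 8 × 0.10 = 1.80; R = √1.40 = 1.183; type I error = 2 × (1 − Φ(1.657)) = 9.8%; power = Φ(0.60/0.2494 − 1.96) = Φ(0.445) = 0.672.

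| m | ICC | DE | R | Type I error | Power |
|---|---|---|---|---|---|
| 3 | 0.01 | 1.02 | 1.005 | 5.1% | 0.808 |
| 3 | 0.05 | 1.10 | 1.025 | 5.6% | 0.793 |
| 3 | 0.10 | 1.20 | 1.049 | 6.2% | 0.774 |
| 5 | 0.01 | 1.04 | 1.010 | 5.2% | 0.805 |
| 5 | 0.05 | 1.20 | 1.049 | 6.2% | 0.774 |
| 5 | 0.10 | 1.40 | 1.095 | 7.4% | 0.738 |
| 9 | 0.01 | 1.08 | 1.020 | 5.5% | 0.797 |
| 9 | 0.05 | 1.40 | 1.095 | 7.4% | 0.738 |
| 9 | 0.10 | 1.80 | 1.183 | 9.8% | 0.672 |

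**Step 3: check site separately.** TAU is drawn from the same locations, so the formula in step 2 does not apply to site. A simulation with 5 sites, 45 per arm, site ICC 0.02 to 0.10 and site left out of the model gave these type I errors:

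- conditions balanced across sites: 0.050 down to 0.043;
- TAU drawn from only 3 of the 5 sites: 0.056 to 0.074;
- balanced, but with an SP effect that varies by site (variance equal to the site variance): 0.059 to 0.090.

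The direction of the site effect thus depends on imbalance or on a varying effect, and the article gives no numbers per site.

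**The case against.** The strongest reply is that the size is unknown. With groups run by diverse community facilitators and the choice left to participant and link worker, few study participants may share a group; at m = 3 and ICC 0.01 the type I error is 5.1%, which is negligible. This stands, and it makes the finding conditional. The power figures are also a yardstick on the plan's own two-group calculation, not the power of the condition-by-time test. The ICC that matters there is the one for 8-week change, because stable group differences already present at T1 cancel.

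A second reply is that random-effect structure is usually left to an analysis plan. That would hold if the article were silent. It lists the structure of the primary models and, in the same section, assigns the nesting to the other model.

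A reader might infer more than the article supports:

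- *That the SEM accounts for sites and the MMRM does not.* The SEM nesting is by group program; no analysis names site.
- *That leaving out site must shrink the standard error.* With conditions balanced across sites it is neutral or slightly conservative (step 3).
- *That condition-by-time is missing from the plan, or that calling condition a level is an error of substance.* Power calculation plans a 2 × 2 mixed analysis of variance, which contains that interaction. This is wording.
- *That TAU should be recruited from the same localities.* Design and participants already plans this.

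**Conclusion.** The point holds in a limited form. The primary MMRM as stated omits a clustering that the same section recognises and that the trial's theory predicts. Because it exists in the SP arm only, the standard error of the SP effect is too small whenever 8-week outcomes are positively correlated within groups. For 3 to 9 study participants per group and ICC 0.01 to 0.10, both assumed, the standard error is understated by a factor of 1.005 to 1.183 and a nominal 5% test has a true error of about 5.1% to 9.8%. Power at d = 0.60 falls from about 0.80 to as low as about 0.67. Site is a lesser matter: allocation is non-randomised and SP also runs at community centres while TAU comes from GP clinics, so the site mix may differ by condition, but the article does not show that it will.

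**What to change.** Carry the SEM's nesting into the primary MMRM. State fixed effects for condition, time and condition by time, the within-participant covariance, and a partially nested random effect for group program in the SP arm. Each TAU participant, and any SP participant who joins no group, counts as a cluster of one. Where someone joins several groups, the first can define the cluster, as it already does for the identification measure.

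The group-program effect must act on the T2 outcome or on change. A group intercept that is constant over time would largely cancel from the condition-by-time contrast and leave the problem in place. Use small-sample degrees of freedom such as Kenward-Roger or Satterthwaite.

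Include locality as a fixed effect, with its interaction with time for the same reason.

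The cost is small. The SEM already needs group membership to be recorded. Intervals widen by about 0.5% to 18% over the range above, and with few groups the group-program variance may be imprecisely estimated, which should be reported alongside the result.

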**Methods:**

Ninety participants experiencing loneliness recruited from primary care services and community centres across five sites in Southeast Queensland will be assigned to one of two conditions (SP, TAU) and assessed at two timepoints (baseline, + 8 weeks). Individuals will be aged 18 years and over, have sufficient English language skills to provide consent, and at the time of recruitment they will not be experiencing acute symptoms or social issues that require urgent intervention. Primary outcomes are loneliness, mental well-being, and health service use (total number of GP, hospital, and allied health visits in the past 3 months). Secondary outcomes will assess social group processes, including number of important social groups, new group identification, multiple identity compatibility, and group-based support and emotion regulation.

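### The structural equation model is said to test relationships over time and mediation, but measures that refer to the new group cannot be placed before the outcomes in a two-survey design

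*Protocol article*

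**What the plan says.** The Abstract states that participants are "assessed at two timepoints (baseline, + 8 weeks", and Data collection confirms the single follow-up: "Participants will then be followed up 8-weeks later (T2". At T1, SP participants "are yet to attend a group or have only recently started attending a group activity". For the primary outcomes, Measures says that "these will be assessed in both T1 and T2 surveys". No equivalent sentence gives the wave of each process measure.

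The process measures are of two kinds. Some refer to the group joined through the programme. Identification is "Social identification with the (first) new group that the participant has joined through the social prescribing program", the first compatibility item reads "Being a member of my new group/s is compatible with being a member of my other groups", and both support items also ask about the new group. Others do not need a new group: the number of important groups, interpersonal emotion regulation, and the second compatibility item, which asks about the participant's groups in general.

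The Analysis section says that the structural equation model is "to test relationships across time between group membership, new group identification, old and new group compatibility", together with help given, emotion regulation and the three outcomes. The Discussion expects improvements "to be mediated by new group identification, old and new group compatibility, and group based psychological resources which are gained". The last paragraph of the Background makes testing these processes the second aim of the study.

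**The concern.** A claim that a variable mediates an outcome needs the variable to come before the outcome, or at least a design that can separate the two directions. Here a person who becomes less lonely for any reason may then feel closer to the new group and report more support from it. A model with an arrow from identification to loneliness would count that as support for the mediation pathway. At stake is what the study may conclude about how SP works, which is one of its two stated aims. Whether SP does better than treatment as usual is a separate question and is not touched.

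**Working it through.** **Figures in the plan.** The article gives no figure for the structural equation model. Its only design figure is 90 participants for the primary outcomes. That reproduces as a two-group F test: with f = .30, the noncentrality is 90 × 0.30² = 8.1 on (1, 88) degrees of freedom, and power is 0.804. The point below does not depend on it.

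**Step 1: when each variable can be observed.** This sets Data collection beside the item wording in Measures.

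| Variable | Needs a new group? | Usable value at T1? |
|---|---|---|
| Loneliness, wellbeing | No | Yes, T1 and T2 stated |
| Number of important groups | No | Yes, if asked |
| Interpersonal emotion regulation | No | Yes, if asked |
| Compatibility, second item | No | Yes, if asked |
| Compatibility, first item | Yes | Not for those yet to join |
| New group identification | Yes | Not for those yet to join |
| Support given and received | Yes | Not for those yet to join |

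Participants who have only just started a group at T1 could answer the last three rows. Those answers would be early impressions given after exposure had begun, and the article does not say how many such participants to expect.

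**Step 2: which paths can be lagged.** For the first compatibility item, identification and support, the established value comes from T2. Loneliness and wellbeing at T2 come from the same survey, and no wave lies between. Health service use is weaker still. Measures counts visits during the study, and the Abstract counts them over the previous 3 months. On either definition the T2 count looks back over visits made before the T2 rating of the new group.

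**Step 3: does adjustment for the T1 outcome settle direction?** Write L1 and L2 for loneliness at T1 and T2, and M for a new-group measure at T2. The forward model factors the data as f(M | L1) × f(L2 | L1, M). The reverse model factors them as f(L2 | L1) × f(M | L1, L2). Both products equal f(M, L2 | L1), so with linear normal models the fit is identical.

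The test of the path is identical too. In either direction t = r√(n − 3) / √(1 − r²), where r is the partial correlation of M and L2 given L1. This is symmetric in M and L2. As an illustration with n = 45 (the planned SP group) and an assumed r of size 0.3, t = 0.3 × √42 / √0.91 = 0.3 × 6.481 / 0.954 = 2.04, whichever variable is called the outcome. A numerical check at n = 45 agreed: forward and reverse models rejected equally often, and their log-likelihoods differed by less than 1e-13.

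Neither fit nor significance can therefore tell the two directions apart when M and L2 share a wave.

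**The case against.** **The waves of the process measures are not restricted to T2.** This stands. A reader might infer that the new-group measures exist only at T2, but nothing in the article says so. The repeated-measures models planned for the secondary outcomes imply both waves, and some participants may already have started a group at T1. The supportable statement is narrower: participants yet to join a group have no new-group value at T1, and values from recent joiners do not precede exposure.

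**Not all process paths are same-survey.** This also stands. It is tempting to say that every path from mediator to outcome is cross-sectional. The number of important groups, emotion regulation and the second compatibility item can be measured at T1 and related to T2 outcomes, and for them the across-time wording is accurate.

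**The model figure, the design figure and any analysis plan are not at hand.** They may well give the waves and the exact paths, and their absence is no fault. But the number of surveys and the item wording are fixed in the article, and no modelling detail can put an order on two variables taken from one survey.

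**Mediation is stated as an expectation, not a conclusion.** This is fair as far as it goes: the Background also uses softer language about processes being implicated. Even so, the Analysis section promises a test across time that names new group identification, and the design cannot supply that test.

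**A false-positive rate could be attached.** A reader might want one. Any such figure would only be the power to detect whatever partial correlation is assumed. The article gives no value for it, so none is offered here.

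**Conclusion.** The concern holds for the measures that refer to the new SP group: identification, support given and received, and the first compatibility item. For these, the model can estimate an association at T2 adjusted for the T1 outcome. It cannot show that the measure came first or that improvement was mediated by it. For the process variables that need no new group, relationships over time can be tested.

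The conclusion rests on the two-survey schedule, the stated timing of T1 and the wording of the items, not on any assumed correlation. Its size is a restriction on what may be concluded under the second aim. The estimates for loneliness, wellbeing and health service use between SP and treatment as usual do not change. The change should be made before results are written up, but it is not critical to the primary comparison.

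**What to change.** 1. In Analysis, describe the paths from new-group measures to outcomes as T2 associations adjusted for the T1 outcome. Keep the across-time wording for process variables with T1 values that do not need a new group: number of important groups, interpersonal emotion regulation and the second compatibility item. Compatibility is planned as the average of two items, so a lagged path would have to use the second item alone.
2. In the last paragraph of the Background and in the Discussion, state that the new-group results will be interpreted as associations consistent with the extended social identity model of identity change, not as evidence of mediation or temporal order.
3. If a reverse-direction model is reported at all, present it only to illustrate that the data cannot distinguish the two directions. It does not test direction.

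The cost is wording. No extra survey, participant or required analysis is involved. The downside is a weaker claim about process.
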